### Data collection and sources of data

Once patients are informed and randomly assigned to one group, we will be able to collect data for statistical analysis. This data collection will take place in the period from October 2016 to March 2017. An independent evaluator in the rehabilitation services will conduct initial assessment and the different measures at 4, 8 and 12 weeks. The data will be added to the database created for that purpose and administered by the principal investigator for statistical analysis.

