### Statistical analysis

The trial results will be presented as a summary of the outcomes in each group, along with the estimated effect size and its precision. The statistical analysis will be performed in accordance with both an intent-to-treat analysis and a per-protocol analysis to have the maximum information about the treatment outcomes.

Frequency tables and histograms will present affiliation data for the participants. We will carry out a descriptive statistical analysis of the different variables, using frequency tables, bar charts and sector charts with the aim of having as much information as possible for exploration and analysis.

The study’s central hypothesis will be tested by comparing change in the CM score between the two groups for the intervention shoulder Appendix 1. To compare independent variables between the two groups, the Student’s *t* test will be used if validity criteria are met; otherwise, we will use the non-parametric approach Appendix 2. As other studies have shown [45], significant departures of normality are not expected. The difference in the evolution of the CM score between treatment groups from baseline to 4, 8 and 12 weeks follow-up will be tested using repeated measurements analysis of variance.

A non-inferiority study seeks to determine whether a new intervention is therapeutically equivalent, or not less equivalent, to an existing intervention reference [46]. In this study, the new intervention TR will be compared with the conventional standard of rehabilitation after SIS in Spain.

Studies have presented results on the minimal clinically important differences for shoulder outcome measures (Fig. 2) [47, 48]. Recently, a study showed minimal detectable change ≥10 points in the CM score and a standard deviation (SD, 11.2) for patients with SIS [45]. Therefore, the non-inferiority criteria will be evaluated comparing the differences between groups with a non-inferiority margin of 10 points in the CM score, which is considered to be a clinically relevant change [49, 50].

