**Fig. 2 Fig2:**
[figure not shown]
Example of customized telerehabilitation programme

Based on these data, we performed a calculation of the sample size. According to [45], an SD of 11.2 in the improvement of the CM would be expected. Anticipating a non-inferiority difference of 10 points on that test, a 90% power and the usual significance level of 5%, a sample size of 22 patients per group is needed. Anticipating a dropout rate of 15% (which will be studied by intention to treat), a total of 44 patients will be included (*n* = 44).

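### Run as standard, neither named test keeps the expected 15% dropouts in the intention-to-treat analysis, and 44 patients leave no allowance for losing them

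*Protocol article*

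**What the plan says.** The Statistical analysis section of the protocol article commits to analysing the trial "in accordance with both an intent-to-treat analysis and a per-protocol analysis". It then names two procedures for the CM score.

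- Central hypothesis: "The study’s central hypothesis will be tested by comparing change in the CM score between the two groups". The next sentence says that "the Student’s *t* test will be used if validity criteria are met", with a non-parametric test as the fallback.
- Course over time: the between-group difference in CM from baseline to weeks 4, 8 and 12 "will be tested using repeated measurements analysis of variance".

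Non-inferiority is to be judged "with a non-inferiority margin of 10 points in the CM score". That sentence does not say at which visit.

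Under Data collection and sources of data, an independent evaluator "will conduct initial assessment and the different measures at 4, 8 and 12 weeks", so a fully observed patient has four CM scores. The sample-size paragraph after the Fig. 2 caption arrives at 22 patients per group and continues: "Anticipating a dropout rate of 15% (which will be studied by intention to treat), a total of 44 patients will be included".

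**The concern.** The sample-size paragraph does not inflate for dropout. It relies on intention to treat to keep the dropouts in the analysis, so the analysis method has to be one that can keep them.

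The classical repeated-measures ANOVA needs a complete row for each patient. Run as standard, it discards a patient lost after week 8 although three CM scores exist. The t test on change is more forgiving of a missed week-4 or week-8 visit, but a patient who leaves before week 12 has no 12-week change score and is omitted there too.

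Two things are at stake. One is precision, since the planned number assumes that nobody is lost. The other is the pairing of intention-to-treat with per-protocol analysis, which is meant to give two different views of a non-inferiority question. If both rest largely on completers, they can share the same bias.

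Unequal loss is conceivable. Under Intervention, the telerehabilitation (TR) group has three 30-minute videoconferences and then exercises alone, while the physiotherapy (PT) group has one-to-one treatment in a 12-week, 5-days-a-week programme. The Discussion also foresees technical difficulties with the videoconferences. If patients doing badly left the TR group more often, the completers in that group would look better than the group as randomised.

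**Working it through.** **Inputs.** From the Statistical analysis section and its sample-size paragraph: margin 10 CM points, SD of improvement 11.2, power 90%, significance level 5% (sidedness not stated), 22 per group, 44 in total, dropout 15%. Assumed, because the article gives no value: true difference 0.

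**1. Reproduce the plan's figure.**

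n per group = 2 × (z₁₋α + z₀.₉₀)² × SD² / margin²

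- One-sided 5%: 2 × (1.645 + 1.282)² × 11.2² / 10² = 21.5, rounded up to 22. This reproduces the article.
- One-sided 2.5%: 2 × (1.960 + 1.282)² × 11.2² / 10² = 26.4, rounded up to 27. This does not.

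The stated 22 therefore matches a one-sided 5% test with a true difference of 0.

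**2. Is dropout allowed for?** 2 × 22 = 44, the number to be included, so there is no allowance. Keeping 22 completers per group with 15% loss would need 22 / 0.85 = 25.9, so 26 per group and 52 in total.

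**3. What is left if dropouts are not retained.** Expected losses are 44 × 0.15 = 6.6, that is 6 to 7 patients. Remaining: 44 × 0.85 = 37.4, or 18.7 per group.

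**4. Power against the 10-point margin.** Power = Φ(margin / SE − z₁₋α), with SE = SD × √(2/n).

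- n = 22: SE = 11.2 × √(2/22) = 3.377; 10 / 3.377 = 2.961; 2.961 − 1.645 = 1.316; power 90.6%.
- n = 18.7: SE = 11.2 × √(2/18.7) = 3.663; 10 / 3.663 = 2.730; 2.730 − 1.645 = 1.085; power 86.1%.

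| Test level | Method | 22 per group | 18.7 per group |
|---|---|---|---|
| One-sided 5% | normal | 90.6% | 86.1% |
| One-sided 5% | noncentral t | 89.8% | 84.9% |
| One-sided 2.5% | normal | 84.2% | 77.9% |
| One-sided 2.5% | noncentral t | 82.5% | 75.7% |

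**5. Which patients each test keeps, without imputation.**

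| Patient | Repeated-measures ANOVA | t test on 12-week change |
|---|---|---|
| All four scores | kept | kept |
| Missed week 4 or 8, seen at week 12 | lost | kept |
| Left before week 12 | lost | lost |

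The last row is the dropout that the sample-size paragraph has in mind, and neither test retains it.

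**6. Bias from unequal dropout.** If dropouts do g points worse than completers in both groups, the completer difference exceeds the full difference by g × (d_TR − d_PT), where d is the dropout proportion. With equal dropout this is 0. With assumed rates of 20% and 10% and g = 10 it is 10 × (0.20 − 0.10) = 1 point in favour of TR. The article supplies neither g nor the rates by group, so this shows the direction and does not estimate the bias.

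**The case against.** The strongest reply has four parts.

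- **No contradiction in the text.** A reader might infer that the ANOVA drops every patient with a missed visit and so contradicts the intention-to-treat promise. The article nowhere says that patients are deleted. Imputing first, or fitting the repeated-measures model by likelihood, would keep them, and such a rule may stand in a full protocol, analysis plan or appendix that is not shown. This stands. The absence of a missing-data rule from a journal article is not itself a fault, and what remains is a tension between a named method and a stated commitment.
- **The F test does not carry the central hypothesis.** A reader might fault the group-by-time test for giving no 12-week difference to set against the margin. The article assigns the central hypothesis to the comparison of change in CM, judges non-inferiority on group differences, and promises an effect size with its precision. This also stands, and that criticism of the ANOVA is not made here. It does not rescue the plan, because the t test on 12-week change loses the same dropouts.
- **The size is moderate or assumed.** The power loss at one-sided 5% is 4.5 points by the normal approximation (90.6 − 86.1) and 4.9 by the t (89.8 − 84.9). It presumes that every dropout lacks a week-12 score, whereas someone who stops treatment might still be assessed. The 1-point bias is an assumption and only a tenth of the margin. All of this stands.
- **The remedy is partly a matter of choice.** Imputation followed by an analysis of covariance could also honour intention to treat, and a mixed model does not remove bias when dropout depends on unobserved poor results. This is true, and it is why the fix includes a sensitivity analysis.

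**Conclusion.** The point holds as a mismatch between method and commitment. Run as standard without imputation, neither the repeated-measures ANOVA nor the t test on 12-week change delivers intention to treat for the expected dropouts, and 44 patients contain no allowance for losing them.

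With 15% lost, about 37 patients remain and power is about 85–86% at one-sided 5% instead of 90%. If the 5% is meant as two-sided (one-sided 2.5%), power is about 76–78%, down from 82–84% with all 44. These figures rest on a true difference of 0, an SD of 11.2, equal loss in both groups and no week-12 score for any dropout.

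The intention-to-treat and per-protocol results could then both rest largely on completers. The documents do not support saying that the result will be biased, or by how much, because they give no dropout rates by group and no outcomes for dropouts.

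**What to change.** Analyse CM at weeks 4, 8 and 12 with a likelihood-based mixed model for repeated measures. Include treatment, visit, treatment-by-visit and baseline CM, with unstructured covariance and small-sample (Kenward–Roger) degrees of freedom, in all randomised patients with any follow-up score. Make the week-12 treatment contrast (TR minus PT) the non-inferiority test, and compare its lower confidence limit with −10. Keep the per-protocol analysis as planned.

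Add one sensitivity analysis that imputes week-12 values and makes them progressively worse for TR dropouts, up to the 10-point margin. It should include patients with no follow-up score, who add nothing to the main model.

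The cost is slightly more analysis work and a missing-at-random assumption, which the sensitivity analysis probes. The visits and measurements are unchanged, and the number randomised stays at 44. The model recovers information from partial follow-up but need not restore the full 90% power; planning for 22 completers per group would take the 52 patients shown in the working.

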**Fig. 2 Fig2:**
[figure not shown]
Example of customized telerehabilitation programme

Based on these data, we performed a calculation of the sample size. According to [45], an SD of 11.2 in the improvement of the CM would be expected. Anticipating a non-inferiority difference of 10 points on that test, a 90% power and the usual significance level of 5%, a sample size of 22 patients per group is needed. Anticipating a dropout rate of 15% (which will be studied by intention to treat), a total of 44 patients will be included (*n* = 44).

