**Methods:**

We will compare an intervention group receiving videoconferences and a telerehabilitation programme to a control group receiving traditional physiotherapy intervention in a single-blind, randomized controlled non-inferiority trial study design.

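### The 15% dropout allowance is stated but not applied: the total of 44 is 2 × 22 evaluable patients, so the claimed 90% power falls to about 85%

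*Protocol article*

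**What the plan says.** The protocol article describes a "single-blind, randomized controlled non-inferiority trial study design". Under Statistical analysis, "The study’s central hypothesis will be tested by comparing change in the CM score between the two groups", and non-inferiority is judged "with a non-inferiority margin of 10 points in the CM score". The sample-size paragraph, which follows the caption of Fig. 2, takes from a cited study "an SD of 11.2 in the improvement of the CM would be expected" and concludes: "a 90% power and the usual significance level of 5%, a sample size of 22 patients per group is needed". The next sentence reads: "Anticipating a dropout rate of 15% (which will be studied by intention to treat), a total of 44 patients will be included". Statistical analysis also plans both an intention-to-treat and a per-protocol analysis.

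**The concern.** A dropout allowance should make the number enrolled larger than the number needed for analysis. Here the two are equal. Either 22 per group already contains an allowance, or the 15% was announced and left out. The only justification offered is the remark in brackets about intention to treat, and that principle does not replace outcomes that were never measured.

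At stake is the only power statement in the article, which supports the central non-inferiority test. If it is too high, a trial that fails to exclude the 10-point margin will be taken to have had a 10% chance of doing so under equal treatments, when the real chance was greater. Neither the effect estimate nor the risk of wrongly declaring non-inferiority is affected.

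**Working it through.** **Inputs from the protocol article**
- Margin: 10 Constant-Murley points (Statistical analysis).
- SD of the improvement: 11.2 (sample-size paragraph).
- Power 90%, level 5%, sidedness not stated (sample-size paragraph).
- Dropout 15%; 22 per group; total 44, which implies 1:1 allocation (sample-size paragraph).

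**Assumption not in the article:** the true difference between groups is 0.

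**Step 1. Reproduce 22 per group.** By the normal approximation, n per group = 2 × [(z_α + z_β) × SD / margin]².
- One-sided 5%: 2 × [(1.645 + 1.282) × 11.2/10]² = 21.48, rounded up to 22. This is the article's figure. The noncentral t calculation gives 23.
- One-sided 2.5% (two-sided 5%, 95% CI): 2 × [(1.960 + 1.282) × 11.2/10]² = 26.36, rounded up to 27 (28 by t).

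So 22 is reproduced only with a one-sided 5% level, and with no loss.

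**Step 2. Could 22 already include the allowance?** At 90% power and one-sided 5%, 22/0.85 = 25.9, so 26 per group and 52 in total (52 × 0.85 = 44.2 evaluable). At one-sided 2.5%, 27/0.85 = 31.8, so 32 per group and 64 in total. Reaching 22 with the allowance inside needs a planned power of about 85%: 2 × [(1.645 + 1.036) × 1.12]² = 18.04, and 18.04/0.85 = 21.2, rounded up to 22. The article states 90%, so the allowance is not inside 22.

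**Step 3. Power of the design as written.** 44 × 0.85 = 37.4, so about 37 evaluable patients, split 19 + 18. The standard error of the difference is 11.2 × √(1/n₁ + 1/n₂), and the noncentrality is 10 divided by it.
- 22 + 22: SE 3.38, noncentrality 2.96.
- 19 + 18: SE 3.68, noncentrality 2.71.

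| Evaluable | One-sided 5%: t (normal) | One-sided 2.5%: t (normal) |
|---|---|---|
| 22 + 22 | 89.8% (90.6%) | 82.5% (84.2%) |
| 19 + 18 | 84.5% (85.8%) | 75.2% (77.5%) |

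The type II error by t at 19 + 18 is 100 − 84.5 = 15.5% at one-sided 5%, and 100 − 75.2 = 24.8% on a 95% CI, against the 10% implied.

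**Step 4. How far the result rests on the assumed difference and the SD.** With all 44 evaluable, at one-sided 5% by t, a true difference of 1 point against telerehabilitation (10 replaced by 9 in the noncentrality) gives 84%, and an SD of 12 gives 86%. With 19 + 18, the same changes give 77% and 80%. Each lowers power whether or not patients are lost, and the dropout loss comes on top.

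**Step 5. Does intention to treat recover the loss?** The Constant-Murley score gives 40 of its 100 points to range of motion and 25 to abduction strength (Primary outcome measures). An independent evaluator takes the measurements at 4, 8 and 12 weeks (Data collection and sources of data). A patient who has left supplies no 12-week score. Imputation can place that patient in the analysis set but does not restore the missing information.

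**The case against.** The strongest reply is that the article does not define dropout. The bracketed remark could mean patients who stop the programme but still attend assessments; the Intervention section separately records deviations from adherence. On that reading the intention-to-treat set keeps all 44, and power stays at about 90% at one-sided 5%. The article does not say this, however. The Discussion allows patients to give up participation at any time, and the planned per-protocol analysis would lose such patients in any case. What stands is a condition: the shortfall applies if the 15% have no 12-week score.

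Three further points deserve weight.
- The figures for a 95% CI rest on a level that the article does not state, and one-sided 5% reproduces 22. They are therefore conditional, and the dropout error stands without them.
- The dropout effect alone is modest, about 5 percentage points, and the step 4 variations in the assumed difference and SD cost about as much. That is a reason for caution about any single power figure. It does not make 44 consistent with a 15% allowance.
- The article promises the effect size with its precision, so readers can judge an inconclusive result directly. This softens the harm but does not correct the stated power.

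**Conclusion.** The point holds. 22 per group is the number needed with no loss, and the total of 44 contains no allowance for the 15% dropout that the same paragraph expects. If those patients have no 12-week Constant-Murley score, power at one-sided 5% is about 85% (84.5% by t, 85.8% by the normal approximation), not 90%, and the type II error is about half as large again as stated. If a 95% CI decides the result, power is about 82% with no loss and about 75% with 15% loss. All these figures assume a true difference of zero, an SD of 11.2 and equal allocation.

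**What to change.** Replace the sentence on dropout with a statement of this kind: assuming no true difference and an SD of 11.2, 22 evaluable patients per group give 90% power at one-sided 5%; with 44 randomised and 15% without a 12-week score (about 37 evaluable), power is about 85%, or about 75% if non-inferiority is judged on a 95% confidence interval. State which of the two levels applies and keep only the figure that goes with it. Remove the suggestion that intention to treat covers the dropout.

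The cost is one corrected sentence and a less favourable power figure, with no extra patients and no change to the margin or analysis. If the sponsor prefers to keep 90% at one-sided 5%, the matching total is 52, which is 8 more than planned; the article reports that enrolment was still ongoing.

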## Discussion

Telemedicine promises to improve quality, increase patient access and reduce costs in healthcare [51]. In addition, recent advances in telecommunication technologies have driven the possibility of rehabilitation processes through the Internet [52].

Studies have shown that telerehabilitation is effective in improving clinical outcomes in various diseases and have also found a strong positive effect for patients, especially after orthopaedic surgery, suggesting that increasing the intensity provided by the telerehabilitation is a promising option to offer to patients [52]. Shoulder pain is a common cause of sick leave and disability and therefore also results in a high consumption of healthcare resources and lost productivity [6]. This research should provide knowledge about the possibility of a new approach for the care of patients operated on for SIS, identifying telerehabilitation effectiveness and the patients’ level of satisfaction in order to finally analyse health resources and costs allocated to defining new policy intervention in this group of patients.

In contrast to other studies that require software implementations on specific devices, our intervention will generate few obstacles, as it is available on any device that allows Internet access, which patients usually have (desktop, laptop, tablet, smartphone). It thus allows access from different devices at any location. This contrasts with other studies that require highly complex technology platforms, software installation and multidirectional cameras for clinical control connecting the physical therapist and the patient [53]. Potential issues in the conduct of this study are the occurrence of selection bias and information. This study only includes individuals who have devices and access to the Internet. Future research should be undertaken to analyse whether individuals without access to the Internet have a different outcome. This research does not provide verification of socio-demographic and affiliation data provided by the participants, so we must assume reliability criteria for the information that they provide. Regarding the technological use, although videoconferences are widespread communication tools, they may present technical problems (disconnection, device failure) and technological difficulties. However, collaborative people are willing to offer support to patients by phone or email, without having to visit patients at home to install or verify any hardware.

Possible adverse events to be considered are a lack of improvement and positive developments in the range of movement, in terms of pain, muscle strength and function of the operated limb. Performing movements with excess load that cause tendon inflammation and muscle strain should also be considered as adverse events. Patients will be informed about the importance of warning the healthcare professional of any incident or misadventure in their recovery and their right to give up their participation at any time during the research.

### Trial status

Patient enrolment and recruitment are ongoing.

## Abbreviations

CM: Constant–Murley test
PT: Physiotherapy group
SAD: Subacromial arthroscopic decompression
SIS: Shoulder impingement syndrome
SPIRIT: Standard Protocol Items Recommendations for Interventional Trials
SST: Simple shoulder test
TR: Telerehabilitation group
TSUQ: Telemedicine Satisfaction and Usefulness Questionnaire
